### Data sources

To reduce the workload of participating investigators during visits, variables recorded in the eCRF will be limited to those that cannot be accurately retrieved from electronic health records (EHR), which will include both local hospital records and the dataset of the Catalan Health Surveillance System (CHSS), a central database of the Catalan Health System. By the time of submitting the study protocol to the ethics committee, all four study sites have separate and different EHRs. Throughout the following year, all the systems are to be unified into a single one and all the data from the different systems will be migrated. These EHR collect all the data related to the care received in the centers, clinical course, prescription, diagnostic images, laboratory tests, and administration, among others. The CHSS systematically collects and stores healthcare data on health status and resource utilization from all healthcare providers. The CHSS was originally designed for healthcare planning and has an automated validation system to identify internal inconsistencies between variables. Since the CHSS registries are used for control of capitation payments, they undergo external audits to ensure provider payment accuracy [16].

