**Primary outcome**			
Rate of complications^b^ of the baseline disease	A secondary disease, an accident, or a negative reaction (including adverse reactions to treatment) occurring during the course of the baseline disease and usually aggravating the illness.	Measure: events, as recorded in the eCRF. Metrics and aggregation: event rate (i.e., proportion of patients experiencing an event within each arm and the follow-up period).	Investigator-reported in the eCRF Local EHR.

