### Participant timeline

Figure 1 summarizes the participant timeline. All participants, irrespective of the study arm, will be scheduled follow-up visits at a frequency determined by the physician based on the diagnostic and therapy of the baseline disease and will receive a reminder (either SMS or phone call) before each visit. Physicians can schedule and cancel appointments at their discretion. At least three visits should be scheduled in the study setting: the baseline visit (i.e., screening visit), intermediate visits (pre-defined by the physician based on the follow-up needed for managing the baseline condition), and the final visit (i.e., either the follow-up visit closest to 12 ± 2 months after enrollment or before in case of discharge or early discontinuation).

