**Fig. 1 Fig1:**
[figure not shown]
Participant timeline ^a^The frequency of the follow-up visits will be determined by the physician based on the diagnostic and therapy of the baseline disease and will receive a reminder (either SMS or phone call) before each visit. ^b^Either the follow-up visit closest to 12 ± 2 months after enrollment or before in case of discharge or early discontinuation

In addition to voluntary withdrawal, the following situations will lead participants in the remote consultation arms to discontinue the study: a change in their clinical status that requires face-to-face consultation and not following the procedures for remote consultation adequately. Patients allocated in the face-to-face arm will discontinue in case their health status discourages moving to the hospital for follow-up visits. The reasons for ending the study will be recorded in the eCRF.

The study will be temporarily interrupted if the local authorities or healthcare center managers decide to ban or limit face-to-face consultations because of the rapid spread of an infectious agent. This interruption can be partial in case banning face-to-face consultations does not affect all hospital services. The study will resume when face-to-face consultations are restored, and there is enough healthcare activity for adequate recruitment in all study arms. In case of a temporal interruption, the study will be automatically extended for a time that is at least equivalent to the interruption time.

The independent ethics committee can interrupt the study at any time in the advent of risk for participants, and the study sponsor can do it as well because of financial issues.

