### Data management and analysis

All data recorded in the eCRF will be stored in a REDCap platform hosted in a local server. The REDCap data will be transferred to a database, which will also contain the data extracted from the local EHR and the CHSS registries. All registries will be linked through the identification number of the Catalan Health Service.

Data recorded in the eCRF will be monitored for completeness and quality by a professional monitor working at the research office of the Hospital acting as sponsor. We will schedule periodic visits to assess the adherence of investigators to the study protocol and good clinical practices. The clinical monitor will release reports at the end of each visit.

A statistical analysis plan, with detailed analyses for each study outcome, will be performed after the last patient has attended the final visit and before the closure of the database.

The primary objective will be assessed using a non-inferiority analysis of the cumulative incidence of complications of the baseline disease between remote consultation (video and teleconsultation arms) and face-to-face consultation, using a non-inferiority margin of 2%. The analysis will be based on a modified binomial test to assess the non-inferiority of an experimental intervention vs. a control group in a three-arm trial [23]. The primary analysis will be conducted on a per-protocol study sample, which will include all participants who have finished the study and have not been withdrawn because of non-allowed visits using modalities other than scheduled. The intention-to-treat population, used for sensitivity analyses, will consist of all randomized patients completing at least one visit. Since the analysis will be based on an event rate, missing data will not be imputed.

The primary analysis will be replicated with patients stratified according to the following characteristics: hospital department, diagnostic, disease duration (chronic vs. acute or sub-acute), anatomic-therapeutic treatment groups, and GMA health risk group. The clinical and demographic characteristics of study participants will be described and compared between excluded/withdrawn participants.

The statisticians will be blinded for the allocation arm. The type I error will be set at 2.5% for the primary analysis and 5% for the rest of the analyses. All analyses will be conducted using R software (version 4.0 or higher) [24]. Data collected during the ECASeT trial will not be re-used.

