The definition of a candidate profile that is suited for remote consultation has been identified among the important challenges of remote consultation deployment [34]. In the research setting, this issue results in difficulty in defining the target population and, therefore, the selection criteria for recruitment. In response to the high demand for remote consultations in our area during the COVID-19 pandemic, the Catalan Health System developed a set of guidelines for helping clinicians and managers of healthcare centers implementing and offering video and teleconsultation appropriately [15, 35]. These guidelines, agreed by different stakeholders, recommend offering remote consultation only to patients without severe or unstable diseases. While these criteria exclude patients at higher risk of experiencing complications, they are unlikely to be offered remote consultation in the real world. Therefore, including them might result in a biased view of the safety of remote consultation in routine practice. Nevertheless, the applicability of the results obtained from our study shall be constrained to candidates to be followed up by remote consultation according to the local guidelines. Briefly, these guidelines identify as candidates all patients without severe diseases who are predisposed to contact the physician remotely.

Aside from the little precedent for making decisions on trial design, our study is challenged by the huge sample to be enrolled for achieving enough statistical power for a primary outcome that is expected to occur in a low frequency. Although the assumptions for sample size calculation will be revised in an interim analysis, as proposed by ICH E9 guidelines [29], recruiting such a huge number of patients is among the main risks of trial success. The risk of not reaching a sample size high enough for a powered analysis might be worsened by other aspects aside from recruitment, including a lower frequency of the primary outcome than expected, short follow-up periods established by the clinician, and high frequency of arm switch because of care needs.

In summary, the study protocol of this RCT, which is novel in assessing the safety of remote consultation as a primary endpoint in general consultations and with powered sample size, provides design insights that will hopefully aid researchers in making decisions in future trials for assessing remote consultation.

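### The primary endpoint is a crude proportion over follow-up of no fixed length, with arm-specific stopping rules and no handling of missing data, so the 2% non-inferiority comparison can be biased

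*Protocol article*

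**What the plan says.** Table 1 gives the primary metric as an "event rate (i.e., proportion of patients experiencing an event within each arm and the follow-up period". The Participant timeline section places the final visit at "either the follow-up visit closest to 12 ± 2 months after enrollment or before in case of discharge or early discontinuation". The same section states that all participants, "irrespective of the study arm, will be scheduled follow-up visits at a frequency determined by the physician".

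The stopping rules, also under Participant timeline, are specific to each arm. Beyond voluntary withdrawal, remote participants leave the study for "a change in their clinical status that requires face-to-face consultation and not following the procedures for remote consultation adequately". Face-to-face participants leave if their health makes travel to the hospital inadvisable. The Interventions section also removes remote participants who require a face-to-face visit from the per-protocol analysis, while controls may have up to 25% of their contacts by phone.

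Under Data management and analysis, the article calls the outcome a cumulative incidence but tests it with a modified binomial test against a 2% margin. The primary set is per-protocol: participants who finished and were not withdrawn for non-allowed visits. The intention-to-treat (ITT) set, used for sensitivity, is everyone randomised with at least one visit. On missing data the section says only: "Since the analysis will be based on an event rate, missing data will not be imputed".

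The Discussion confines the screening of electronic health records (EHR) to the follow-up period. It mentions "short follow-up periods established by the clinician", but only as a threat to power.

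**The concern.** A proportion with an event has meaning only together with a length of observation. Here that length varies between patients, the test has no time scale, and record screening stops when follow-up stops. Basing the analysis on an event rate does not remove the missing-data problem. It hides it in the numerator, where an unobserved event counts as no event, or in the choice of who is analysed.

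Two mechanisms follow:

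- **Truncated observation.** This affects the ITT set and early discharges. A patient observed for six months has less opportunity to show a complication than one observed for twelve, yet both count as one in the denominator.
- **Selective exclusion.** This is the main route in the primary per-protocol set. Patients who stop because they deteriorate are dropped, and those who remain look healthier than the arm that was randomised.

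Either mechanism moves the risk difference if it acts unequally on the arms. With a margin of 2 percentage points on a 10% control rate, modest inequality matters to the trial's main safety conclusion.

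**Working it through.** **Inputs from the article (Sample size considerations; Data management and analysis).** Control risk 10%, remote risk 12%, margin 2 points, type I error 2.5% (taken as one-sided), power 80%, 10% lost to follow-up, 1068 per arm.

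**The plan's own figure.** With a common rate of 11% and a distance to the margin of 4 points, n = (1.96 + 0.8416)² × 2 × 0.11 × 0.89 / 0.04² = 961 per arm, and 961 / 0.9 = 1068. The 4-point distance is a separate question; I use the result only to fix 961 analysed per arm.

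**Assumptions not in the article.** Constant hazard, and the stopping shares and exposure fractions below. The article gives no expected exposure by arm.

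**Formulas.**
- Risk p at 12 months, observed over a fraction f of that time: 1 − (1 − p)^f.
- Probability of declaring non-inferiority: Φ((0.02 − d)/SE − 1.96), where d is the expected observed difference (remote minus control) and SE is unpooled with 961 per arm.
- A true 12% v 10% lies on the margin, so with complete 12-month data this probability is 2.5%. Any excess is false non-inferiority.

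**(a) Early stoppers kept as event-free after half the follow-up (ITT set).** A remote stopper shows 1 − 0.88^0.5 = 6.19%; a control stopper shows 1 − 0.90^0.5 = 5.13%. With 10% remote stoppers the arm reads 0.9 × 12% + 0.1 × 6.19% = 11.42%. With 10% control stoppers that arm reads 0.9 × 10% + 0.1 × 5.13% = 9.51%.

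| Remote stoppers | Control stoppers | Observed difference | False non-inferiority |
|---|---|---|---|
| 10% | 0% | 1.42 points | 6.1% |
| 20% | 0% | 0.84 points | 13.0% |
| 10% | 10% | 1.91 points | 2.9% |
| 5% | 10% | 2.20 points | 1.8% |

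The last row shows the bias reversing when more controls stop.

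**(b) Shorter mean remote exposure, full control exposure.**

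| Remote exposure | Remote arm reads | False non-inferiority |
|---|---|---|
| 95% | 1 − 0.88^0.95 = 11.44% | 5.9% |
| 90% | 1 − 0.88^0.90 = 10.87% | 12.6% |
| 80% | 1 − 0.88^0.80 = 9.72% | 38.8% |

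A 12% risk reads as 10% when f = ln 0.90 / ln 0.88 = 0.824, or about 9.9 months.

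**(c) Deteriorating remote patients dropped from the per-protocol set.** Excluding 10% of the remote arm at 24% risk leaves (12% − 0.1 × 24%) / 0.9 = 10.67%, and false non-inferiority is 15.9%. If the excluded patients' risk is 36%, the rest read (12% − 0.1 × 36%) / 0.9 = 9.33%, and the probability is 50.7%.

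**The case against.** A reader might infer that follow-up depends on arm by design and that remote patients will be followed for less time, so that the bias must favour remote consultation. The article does not support this. It sets visit frequency irrespective of arm, and the Outcomes and variables section retrieves the investigator's planned follow-up from the EHR alongside baseline variables. Arm dependence enters only through the stopping rules, and the face-to-face arm has one too.

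A reader might also infer that early stoppers count as event-free in the primary analysis. As written, the per-protocol set mainly drops them. Truncation reaches that set only if an early final visit counts as finishing, which is unclear. A clinical change that ends remote follow-up may also itself meet the broad definition of a complication and be counted.

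The larger exposure deficits in (b) have no source in the article. A mean of 10 months through stoppers at six months would need one third of remote patients to stop and no controls, against a planned loss of 10%. The Data sources section also counts the Catalan Health Surveillance System (CHSS) among EHR sources, so it is not left out of the plan. Finally, an analysis plan not shown here may define censoring.

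These points limit the direction and size of the claim. They do not rescue the no-imputation rationale, nor a proportion taken over unequal observation, both of which the article fixes in its own text.

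**Conclusion.** The concern stands as a risk of bias, not as a demonstrated shift toward non-inferiority. The article fixes a crude proportion, a test without a time scale, follow-up that can end early, health-related stopping rules that differ by arm, record screening that ends with follow-up, and a rationale for ignoring missing data that does not follow. Bias toward non-inferiority is plausible from the remote-arm rules, but it reverses if more controls stop.

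The size depends on unknown stopping patterns. With roughly the planned level of loss, truncation alone moves false non-inferiority from 2.5% to between about 2% and 6%. Larger exposure gaps, or selective exclusion from the per-protocol set, take it to 13% and beyond. All of this rests on a constant hazard, a true 12% v 10%, 961 analysed per arm and the assumed shares.

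**What to change.** Define the primary endpoint as the first complication of the baseline disease within 12 months of randomisation. Ascertain it through month 12 for every randomised participant, whether or not they were discharged, stopped or changed modality, unless consent to data use is withdrawn. The clinical stopping rules need not change; only outcome ascertainment continues beyond them. Use the eCRF, the local EHR and CHSS, which is already to be linked and is described thus: "The CHSS systematically collects and stores healthcare data on health status and resource utilization from all healthcare providers". Align the Local EHR entry in Table 1 with the wider definition under Data sources.

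Estimate the 12-month risk difference by Kaplan-Meier, or Aalen-Johansen if death competes, and test it against the 2% margin. Report it for the randomised population alongside the per-protocol result. Kaplan-Meier alone does not cure informative stopping; complete ascertainment is the essential part. Replace the no-imputation sentence with a sensitivity analysis that assigns higher event rates to remote-arm stoppers.

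The cost is revised wording and a longer data extraction, with no new visits. There are two real downsides. Whether a post-discharge event is related to the baseline disease would be judged from records only. Time after leaving the allocated modality can dilute a true difference, which is itself a risk in a non-inferiority trial and is why both analysis sets should be reported.

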## Design

### Study setting and participants

The ECASeT trial (*Ensayo Clínico abierto y Aleatorizado para valorar la Seguridad de la Teleconsulta, frente a la consulta clínica presencial* in Spanish) is aimed at testing safety of remote consultations, based on its non-inferiority compared with face-to-face consultation. The ECASeT trial will be conducted in four centers in the healthcare area of *Alt Penedès-Garraf* in Catalonia (North-East Spain): three secondary hospitals (Hospital Sant Antoni Abat, Hospital Sant Camil, and Hospital Comarcal de l’Alt Penedès) and a rehabilitation center, all part of Healthcare Consortium Alt Penedès Garraf (CSAPG). All study sites belong to the public network of hospitals and primary care centers of the Catalan Health Service and provide universal healthcare to a catchment population of 247,357 inhabitants. Hospital departments from all areas (i.e., locomotive, internal medicine, surgery, gynecology, and pediatrics) are involved in the study.

Participants will be screened from all individuals, irrespective of age and sex, who require follow-up in outpatient consultations of any of the departments involved in the study. Eligibility criteria have been established based on the local guidelines for screening patients for remote consultation [15]. Briefly, to be eligible for remote consultation, patients have to have adequate digital literacy at the physician discretion and technological capacity to use the video conferencing software and undergo a type of follow-up that, due to the moderate complexity of the pathology, does not require physical examinations. Patients followed up in more than three departments, those with visual or hearing impairments that may hamper patient-physician communication, and those enrolled in another clinical trial that requires an experimental intervention during the follow-up will be excluded from the study.

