### Sample size considerations

The sample size was estimated based on the primary endpoint of cumulative incidence of complications related to the baseline disease. The sample size analysis was computed with R software [24], following the approach described by Steen A. Julious for non-inferiority trials [25]. Although there is little available information regarding this outcome in the general population of chronic patients, we expect 10% of events in face-to-face consultations [26–28] and 12% in the remote consultation arm (based on routine practice of the research team). Assuming a type-I error of up to 2.5% and a statistical power of 80%, 1068 subjects per arm should be analyzed to reject the non-inferiority hypothesis with a non-inferiority margin of 2% and assuming 10% of participants lost to follow-up.

Altogether, the participating centers schedule 252,000 routine follow-up visits during a period equivalent to the study, corresponding to 121,400 different patients. Therefore, the recruitment of the estimated 2136 patients is considered within the capabilities of the participating centers.

Owing to the scarcity and heterogeneity of available data about the primary endpoint, a blinded interim analysis will be conducted when 50% of the total sample has been recruited to revise the assumptions used to calculate the sample size, as proposed in the E9 Guide of the ICH on Statistical Principles for Clinical Trials [29].

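### Repeating the 2%-margin non-inferiority analysis within each level of five baseline factors cannot inform at this sample size and does not test whether the effect varies between subgroups

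*Protocol article*

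**What the plan says.** In the Protocol article, Data management and analysis, the primary objective is one pooled comparison: remote consultation against face-to-face, on the cumulative incidence of complications, with a 2% non-inferiority margin. Subgroups are then handled by repeating that analysis: "The primary analysis will be replicated with patients stratified according to the following characteristics: hospital department, diagnostic, disease duration (chronic vs. acute or sub-acute"), followed by "anatomic-therapeutic treatment groups, and GMA health risk group".

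The same section sets the error rates: "The type I error will be set at 2.5% for the primary analysis and 5% for the rest of the analyses". It does not say whether a replicated primary analysis counts as primary (2.5%) or as part of the rest (5%), or whether the 5% is one- or two-sided.

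The number of levels is clear only for disease duration, which has two. Study setting and participants gives five areas: "Hospital departments from all areas (i.e., locomotive, internal medicine, surgery, gynecology, and pediatrics) are involved in the study". The numbers of individual departments, diagnoses, treatment groups and health-risk groups are not given.

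**The concern.** A non-inferiority test asks whether the confidence limit for the difference lies inside the margin. The 2% margin is demanding even for the whole trial. Applied to a fifth or a half of the patients, the same test mostly reports how few patients are in the level.

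Two errors follow. Most levels in which remote follow-up is just as safe will fail. If remote follow-up is worse by the margin, some levels may still pass by chance, and each added level gives another opportunity. Neither outcome addresses the usual question of a subgroup analysis, which is whether the difference between arms changes across levels. One level passing while another fails is not evidence that they differ.

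The Discussion states the aim as overall safety across conditions seen in a secondary hospital, and Ethical study conduct says the report goes to local healthcare planning authorities. If per-department verdicts were reported, those readers could act on differences that are only noise.

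**Working it through.** **Inputs** (Sample size considerations, unless stated)
- Face-to-face risk 10%: "we expect 10% of events in face-to-face consultations".
- Remote risk 12%: "12% in the remote consultation arm (based on routine practice of the research team".
- Size: "Assuming a type-I error of up to 2.5% and a statistical power of 80%, 1068 subjects per arm should be analyzed", with 10% lost to follow-up. I take 1068 × 0.9 = 961 analysed per arm.
- Margin 2%, read as two percentage points (Data management and analysis).
- Assumed: equal-sized levels, and a normal approximation with unpooled variance in place of the cited modified binomial test.

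**The plan's own figure.** (1.960 + 0.842)² × 2 × 0.11 × 0.89 / 0.04² = 960.5, so 961 per arm, and 961/0.9 = 1068. This reproduces the stated size. It uses a distance of four points, the margin plus the expected difference. For a harmful outcome at 10% v 12% the distance to a two-point margin is zero. That is a separate sample-size matter; here I take only the number of patients.

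**Chance that a truly safe level passes (10% v 10%).** With k equal levels, n = 961/k per arm, SE = √(2 × 0.10 × 0.90 / n), and P(pass) = Φ(0.02/SE − z), where z = 1.645 (one-sided 5%) or 1.960 (one-sided 2.5%).

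| Levels | n per arm | SE | 0.02/SE | P(pass), 5% | P(pass), 2.5% |
|---|---|---|---|---|---|
| 1 (whole trial) | 961 | 0.0137 | 1.461 | 42.7% | 30.9% |
| 2 | 480 | 0.0194 | 1.033 | 27.0% | 17.7% |
| 5 | 192 | 0.0306 | 0.654 | 16.1% | 9.6% |
| 10 | 96 | 0.0433 | 0.462 | 11.8% | 6.7% |

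The first row is a ceiling: at a 10% risk in both arms, no level can pass more often than the whole trial would. The conclusion that most safe levels fail therefore does not depend on equal sizes.

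**What a pass would need.** With five areas, the observed remote-minus-face-to-face difference must lie below about 2 − 1.645 × 3.06 = −3.0 points (one-sided 5%) or 2 − 1.960 × 3.06 = −4.0 points (2.5%). Remote care would have to look three to four points better than face-to-face to be called not worse. The 95% CI half-width is 1.960 × 3.06 = 6.0 points, three times the margin.

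**Chance of a false non-inferior verdict (10% v 12%).** This is the plan's own expectation, and it lies exactly at the margin. Each test then passes with probability equal to its error rate. The five areas contain different patients, so the tests are independent:
- one-sided 5%: 1 − 0.95⁵ = 22.6%
- one-sided 2.5%: 1 − 0.975⁵ = 11.9%

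Ten independent levels would give 40.1% and 22.4%.

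**Would adjusting the error rate help?** Bonferroni over five areas uses z = 2.326 (5%/5) or 2.576 (2.5%/5). P(pass) for a safe area becomes Φ(0.654 − 2.326) = 4.7% or Φ(0.654 − 2.576) = 2.7%. False passes are capped, but the test is even less able to recognise a safe area.

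**The case against.** The strongest reply is that this is a condensed article which leaves detailed analyses to a statistical analysis plan. Exploratory labels, interaction tests and multiplicity rules are routine content there, so their absence is no fault. That stands, and the point does not rest on it. What the article does fix is the method: the non-inferiority analysis is repeated by stratum. That choice is poor whatever label is later attached.

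It can also be said that the article nowhere promises a pass/fail declaration per department, and that failures in safe levels partly reflect the size of the whole trial, which has 30.9% power at 10% v 10% and one-sided 2.5%. Both are fair. The harm depends on how results are reported, and changing the subgroup method does not cure the overall size. But repeating a non-inferiority analysis naturally yields a verdict per level, and the smaller samples make weak power weaker.

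Three stronger readings are tempting, and the document does not support them.
- *False safe verdicts for departments are likely.* For the five named areas the risk is 12% to 23%, and only if every area sits exactly at the margin. With a true four-point excess it is 6.0% (one-sided 5%) or 2.6% (2.5%). Chances above one half need about 14 independent levels at one-sided 5%, and the article does not give the count.
- *Every subgroup test runs at a full 5%.* That is one reading. A replicated primary analysis may carry 2.5%, and a two-sided 5% is one-sided 2.5% for non-inferiority.
- *The eight secondary outcomes in Table 1 form an uncontrolled family of tests.* Table 1 gives summary metrics only and names no secondary test, and handling of multiplicity there belongs to the analysis plan.

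**Conclusion.** The point holds for the replicated subgroup analyses. At the planned size, a per-level non-inferiority test fails in at least 73% of truly safe levels with two equal levels (82% at one-sided 2.5%), and in 84% to 90% with five. At the margin, the chance of at least one false pass among five areas is 12% to 23%, and it is higher with more levels. The ambiguity over error rate and sidedness moves these figures but not the conclusion. Nor do the separate tests show whether the effect differs between subgroups.

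The figures assume 961 analysed per arm, a 10% control risk, equal levels and a normal approximation. A lower event risk would raise the pass rates; exclusions from the per-protocol sample beyond 10% would lower them. The pooled primary comparison is not affected by this point.

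**What to change.** In Data management and analysis, replace the sentence that replicates the primary analysis by stratum with:

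*For each of these baseline characteristics, the remote-minus-face-to-face risk difference with 95% CI will be shown per level, with one arm-by-characteristic interaction test. These analyses are exploratory, and no non-inferiority conclusion will be drawn within a subgroup.*

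This also removes the need to decide which error rate and sidedness govern a within-level non-inferiority test. Carry the same wording into the statistical analysis plan.

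The cost is small: one passage of text and notification of the change, with no new patients or data. The sponsor gives up stand-alone non-inferiority statements for single departments or risk groups, which the sample cannot support. Interaction tests will themselves have limited power, so a non-significant result should not be read as proof that the effect is uniform.
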